### Outcomes

A)Primary outcome:

To evaluate the incidence of delirium and incidence of subsyndromal delirium by applying the CAM [15] twice daily during five days of hospitalisation.

The incidence of basal delirium will be determined before the software is implemented in a group of patients enrolled prospectively with the same inclusion/exclusion criteria and delirium assessment protocol.

B)Secondary outcomes:Duration of delirium (days) and density of delirium (incidence x duration) will be assessed with the CAM.Level of independence in basic activities of daily living on day 5, will be assessed using the Functional Independence Measure (FIM), this instrument evaluates independence in 18 activities of daily living (13 motor and five cognitive items). The scale has seven levels (1–7, from lower to higher levels of independence). The motor FIM score ranges from 13–91, cognitive FIM from 5–35 points, and total FIM from 18–26 points; higher scores indicate greater independence [16].Cognitive level on Day 5 assessed using the Montreal Cognitive Assessment. The test evaluates attention and concentration, executive functions-memory, language, visuoconstructional skills, conceptual thinking-calculations, and orientation. It has Chilean validation in the population over 60 years of age [17].Hospital stay (days).90-day mortality.Duration of device use will be compared using the internal device registration.Presence of sleep disorders and headache will be evaluated using a self-reporting instrument in both groups. The doctor in charge of the patient will be informed for management.Adherence to the nPPD programme will be evaluated in the four participating centres before and after training in prevention measures. Assessment of adherence to non-pharmacological prevention domains (12 indicators) will be conducted [13].

In addition, socio-demographic data and clinical information will be gathered including The reason for admission, the Acute Physiology and Chronic Health disease Classification System II score, the Sequential Organ Failure Assessment), and the Charlson Comorbidity Index.

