### Study sample

Local and literature data were evaluated to calculate the sample size [1, 13]. A delirium status prevalence of 20% is estimated in the control group and a decrease in prevalence to 8% in the intervention group is expected. In this way, with a power of 80%, and an alpha of 0.05 bilaterally, 147 patients will be enrolled in each group. If we add to this a 10% loss of follow-up, the overall sample size will be 320 patients (See flow chart in Fig. 1).

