### Analysis and statistical methods

The results will be analysed with the intention to treat. For the descriptive analysis of the variables, we will use the mean (standard deviation), median (25–75 percentile), or proportions as appropriate to the type and distribution of the data.

Analytical Statistics: For the primary outcome, a comparison of proportions between patients who develop delirium and subsyndromal delirium in both groups will be made, using Fisher's exact test, and as a measure of efficacy, an odds ratio with 95% confidence interval will be estimated. If there is any baseline variable that is not matched by the randomisation, efficacy analyses will be conducted using logistic regression with the main variable being the treatment, and the adjustment variables will be those that the randomisation would not have been able to match. Additionally, to compare the effect of the intervention over time, a time-to-event analysis will be performed using the Kaplan-Maier procedure and then the Cox regression model to adjust for baseline variables and the presence of the intervention. For the secondary outcomes, the Fisher's exact test or t-test will be used, as appropriate for the type and distribution of the data. Linear regression or multivariate logistics will also be performed, as appropriate, to evaluate the impact of the intervention, adjusting for the input covariates. A bilateral *p* < 0.05 significance level will be used for all analyses.

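### The supplementary Kaplan-Meier curves have no place for discharge or death before day 5, so with exits censored they overstate in-hospital delirium and will not match the primary proportion

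*Protocol article*

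**What the plan says.** Under Outcomes, the protocol article defines the primary outcome as the incidence of delirium and of subsyndromal delirium, found "by applying the CAM [15] twice daily during five days of hospitalisation". The same section lists length of hospital stay and 90-day mortality as secondary outcomes.

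Under Analysis and statistical methods, the analysis set is intention to treat, and the main efficacy analysis is worded as follows: "a comparison of proportions between patients who develop delirium and subsyndromal delirium in both groups will be made, using Fisher's exact test". An odds ratio with 95% confidence interval goes with it. As an additional analysis of the effect over time, "a time-to-event analysis will be performed using the Kaplan-Maier procedure and then the Cox regression model".

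Under Study sample, the assumption for one arm reads "A delirium status prevalence of 20% is estimated in the control group"; for the other arm, the article says that "a decrease in prevalence to 8% in the intervention group is expected". It adds 10% for loss to follow-up. The article does not say how a patient who is discharged or dies before day 5 enters either analysis, and it gives no discharge or length-of-stay figures.

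**The concern.** The outcome can be seen only while the patient is in hospital. The population is acute admissions to general wards and intermediate care, so some patients may leave or die within five days. Kaplan-Meier knows two states, event and censored. A patient who exits without delirium can only be censored, and is then treated as someone who would have gone on to develop delirium at the rate of those still on the ward. The resulting curve describes the risk if nobody left. It does not describe how many patients develop delirium in hospital.

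Two things are at stake. First, the published curves would show higher incidences than the primary proportions in the same paper, with nothing to explain the gap. Second, length of stay is itself an outcome, and the Abstract and Background link delirium to longer stay and higher mortality. The time under observation could therefore differ by arm, and a reader needs to see whether it does.

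**Working it through.** **The plan's own figure.** With 20% versus 8%, two-sided alpha 0.05 and 80% power, the mean proportion is 0.14 and n = [1.960·√(2·0.14·0.86) + 0.842·√(0.2·0.8 + 0.08·0.92)]² / 0.12² = 130.1, that is 131 per arm. With the continuity correction, (130.1/4)·[1 + √(1 + 4/(130.1·0.12))]² = 146.3, that is 147, as stated. The 20% is used below.

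**Inputs.** From the article: five days with CAM twice daily, so ten half-day slots; 20% control risk; 147 per arm. Assumed: 20% is the five-day risk if everyone stayed; both hazards are constant; exit is unrelated to delirium risk; a share q would have left by day 5 in the absence of delirium. The article gives no value for q, so a range is shown.

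**Model.** Delirium hazard per slot: h = 1 − 0.8^(1/10) = 0.02207. Exit hazard per slot: d = 1 − (1 − q)^(1/10). Probability of still being at risk after one slot: s = (1 − h)(1 − d), so s^10 = 0.8(1 − q). In-hospital cumulative incidence = h(1 − s^10)/(1 − s). Censoring exits, 1 − Kaplan-Meier = 1 − (1 − h)^10 = 20% whatever q is.

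For q = 20%: s = 0.64^(1/10) = 0.95635, and 0.02207·0.36/0.04365 = 18.2%.

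| Exit by day 5 (assumed) | In-hospital incidence, ten slots | Same, continuous time | 1 − Kaplan-Meier |
|---|---|---|---|
| 20% | 18.2% | 18.0% | 20% |
| 30% | 17.2% | 16.9% | 20% |
| 40% | 16.2% | 15.8% | 20% |
| 50% | 15.1% | 14.6% | 20% |

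The continuous-time column uses λ = −ln(0.8)/5 and δ = −ln(1 − q)/5 in λ/(λ + δ)·[1 − exp(−5(λ + δ))].

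**Unequal exit, no effect on the delirium hazard (ten-slot model).**
- 30% versus 40% exit: 17.2% versus 16.2%; odds ratio (0.162/0.838)/(0.172/0.828) = 0.93.
- 20% versus 50% exit: 18.2% versus 15.1%; odds ratio (0.151/0.849)/(0.182/0.818) = 0.80.
- Fisher's test at 147 per arm rejects in about 4.0% and 8.3% of trials respectively, against 3.6% when both arms have 20%.

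**Per observed half-day.** Expected slots at risk per patient are (1 − s^10)/(1 − s): 8.25 at 20% exit and 6.85 at 50%. Events per slot are 0.1820/8.25 = 0.0221 and 0.1512/6.85 = 0.0221. The rate ratio is 1, as it should be when the hazard is the same.

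**The case against.** The strongest reply is that the primary analysis is sound. "The results will be analysed with the intention to treat", so if every randomised patient is in the denominator and exit without delirium counts as no event, the proportion is a valid cumulative incidence of in-hospital delirium. Without other censoring, the Aalen-Johansen estimate at day 5 equals that proportion, so the new curves would show the same gap between arms and would not remove it. Kaplan-Meier is supplementary. Cox with exits censored still estimates the cause-specific hazard ratio, which unequal discharge alone does not move. All of this stands.

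It is also true that the article states no censoring rule and that such rules often sit in a full protocol or SAP, neither of which is shown. The silence is therefore not the point. The point is that the method named has no place for a competing event.

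A reader might infer more than the document supports:
- **That the primary risks are misstated or biased.** They are not, once read as in-hospital incidence. They depend on length of stay, and a false difference between arms needs exit to differ by arm. No figure in the article shows that it will.
- **That the table above measures informative censoring.** It assumes exit unrelated to risk, so the gap is between two different quantities. If healthier patients leave first, Kaplan-Meier would overstate even the risk had everyone stayed, but that is not quantified here.
- **That time zero is wrong.** The phrase "twice daily during five days of hospitalisation" is loose, since enrolment may come up to 48 h after admission. But delirium is excluded at entry and the tablet is used for five days, so five study days is the natural reading.
- **That the trial is underpowered.** The 20% and 8% may already be in-hospital proportions.

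**Conclusion.** The concern holds for the supplementary Kaplan-Meier analysis. For an outcome seen only in hospital, with exits censored, 1 minus Kaplan-Meier exceeds the in-hospital incidence by about 2 to 5 percentage points when 20% to 50% leave by day 5, starting from 20%. These sizes rest on an assumed exit share, constant hazards and exit unrelated to risk; with few early exits the gap is small.

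The primary Fisher comparison should stay, with its meaning made explicit. Its sensitivity to unequal discharge is modest: an odds ratio of about 0.93 for a 10-point difference in exit and 0.80 for a 30-point difference, against a design odds ratio of (0.08/0.92)/(0.20/0.80) = 0.35. That justifies a sensitivity analysis, not a change of primary analysis.

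**What to change.** 1. Replace the Kaplan-Meier curves with Aalen-Johansen cumulative incidence of delirium status by arm, from randomisation to day 5, with discharge alive and death as competing events.
2. Keep the Cox model, report it as a cause-specific hazard ratio, and show the cumulative incidence of discharge by arm beside it.
3. Keep Fisher's test on all randomised patients as the primary analysis, and state that the proportion is the cumulative incidence of in-hospital delirium status, which depends on length of stay.
4. As a sensitivity analysis, compare arms per CAM-observed half-day, for example by Poisson regression or a complementary log-log model with an offset for observed slots.

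If an SAP already contains these rules, a sentence in the protocol is enough. Hospital stay and 90-day mortality are already outcomes, so the cost is a little more analysis work. The choice should be fixed before unblinding, so that nobody chooses afterwards between two analyses that can disagree.

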## Discussion

The implementation of non-pharmacological prevention strategies for delirium is still rare in hospitals. This clinical trial seeks to enhance the implementation of these measures through the use of cognitive software (PREVEDEL) that allows older adults admitted to intermediate critical units and general rooms, to keep their cognitive functions active, promote early mobility, and the use of sensory devices to reduce the incidence of delirium and subsyndromal delirium. The use of PREVEDEL can increase the access to delirium prevention in hospitals, since there may be several patients using it simultaneously: relevant aspect in units with highly demanded professionals and with difficulties in the implementation of prevention measures [14, 18].

PREVEDEL is a software that has already tested its accessibility, usability, and acceptability in older adults, we will validate its use in this clinical trial [12].

Finally, if the results of this clinical trial are positive, it will be of great use to hospitalised patients and health professionals.

## Data Availability

Data sharing is not applicable to this article as no datasets were generated or analysed at this stage of the study. Once the study protocol is published, it will be shared and disseminated through clinical dissemination sessions (health personnel, undergraduate and postgraduate students) and on the website of the participating hospitals.

## Abbreviations

nPPD: Non‐pharmacological interventions to prevent delirium
RCT: Randomized controlled trial
HCUCH: Hospital Clínico de la Universidad de Chile
HSJD: Hospital San Juan de Dios
CLC: Clínica Las Condes
HLT: Hospital Santiago Oriente [name]
CAM: Confusion Assessment Method
AD8: Alzheimer Disease
FIM: Functional Independence Measure
TSC: Trial Steering Committee
FONDEF: Fondo de Fomento al Desarrollo Científico y Tecnológico
